### Measures

#### Clinical and Demographic assessment

1) Sociodemographic data will be obtained based by using an adapted form of the CIDI sociodemographic section;

2) Structured Clinical Interview for DSM-IV (SCID) I: SCID is a semi structured interview for the DSM-IV [71,72]. It allows the diagnosis of mental health disorders according to DSM IV criteria and has already been validated for Brazilian population [73];

3) Clinician Administered PTSD Scale (CAPS) [74]: A clinician rating scale for assessing current and lifetime PTSD: the CAPS-1. CAPS is a structured clinical interview designed to be applied by clinician and its validation was included as part of the first phase of this protocol. It is a 30 items scale investigating the frequency and intensity of PTSD symptoms and traumatic life experiences.

4) Beck Anxiety Inventory (BAI): BAI is a self-administered 21 items questionnaire assessing intensity of anxiety symptoms [75];

5) Beck Depression Inventory (BDI) is used to assess depressive symptoms in clinical settings [108]; it is a self-administered 21 items questionnaire, and it has been validated for the Brazilian population [76];

6) Global Assessment of Function (GAF) scale provides data on the clinical global state of patients [77];

7) The Social Adjustment Scale (SAS) is a self-administered instrument to assess social adaptation [78,79] and it has been validated to the Brazilian social and cultural context [80];

8) Medical Outcomes Study 36-Item Short-Form Health Survey (MOS SF-36) [81] is a self-report scale constructed to collect data on health status, functioning, and well-being. A Portuguese version of the questionnaire has already been tested for its validity and reliability in Brazil [82];

9) Early Trauma Inventory (ETI) is a semi-structured interview comprising 56 items to measure traumatic life experiences occurred in early life, in the following domains: sexual, physical and psychological abuse and other traumatic life experiences [83];

10) Clinical global Impressions (CGI) is a scale to assess treatment response in patients with mental disorders [84];

11) Peritraumatic Dissociative Experiences Questionnaire (PDEQ) [85] is a reliable and valid measure of peritraumatic dissociation as previously described in the epidemiologic study section.

#### The Neuropsychological Assessment

The neuropsychological evaluation will be performed in a single session by neurophysiologists trained in the instruments listed as follows. The training has been conducted by a senior psychologist, acquainted to the assessments chosen for the study, who will be responsible for supervising the trainees in order to keep the accuracy of measurements. The following tests will be part of the Neuropsychological Assessment:

1) The Wisconsin Card Sorting Test (WCST) will be used to assess cognitive set shifting and executive functions [86];

2) Vocabulary and Blocks – Subscales WAIS III is a widely used measure for intellectual level[87];

3) The Digit Span – Subscale WAIS III is an important tool for evaluating working memory and short-term memory[87];

4) The Spatial Span – Subscale WMS III is meant for assessment of immediate nonverbal memory and nonverbal working memory[87];

5) The International Affective Picture System (IAPS) was validated in Brazil and measures visual memory and emotional reaction through positive, negative and neutral figures [87];

6) The Rey Auditory-Verbal Learning Test (RAVLT) assesses the verbal learning and memory [88]

7) The Stroop Test is designed to assess selective attention and cognitive flexibility[89]

8) The Visual Reproduction – Subscale WMS III assess visual memory[87];

9) Cancellation of Mensulan assesses selective visual attention, vigilance and visual neglect[90];

10) Social and Occupational Functioning Assessment Scale (SOFAS) [1] – Assess the social and occupational functioning in the community.

#### Magnetic Resonance Imaging

Imaging data will be acquired at the Instituto do Sono, Federal University of Sao Paulo, using a GE1.5-T Signa scanner. Structural MR images will be acquired using a sagittal T1 acquisition series (TR = 9.8 ms, TE = 3.1 ms, flip angle = 30°, NEX = 1, matrix size = 256 × 256, FOV = 24 cm, thickness = 1.0 mm). A T2-weighted image series will also be acquired. Before scanning, a sagittal scout series (nine to eleven 5-mm-thick slices with a 1-mm interslice gap) will be performed to determine image quality and clarity as well as subject head position. Measurements will be conducted on PC workstation with the aid of BRAINS2 software [91]. Before tracing, T1- and T2-weighted images will be spatially realigned so that the brain anterior-posterior axis is parallel to the intercommissural line, which was horizontal in the sagittal plane, and the interhemispheric fissure is vertical in the axial plane. Six brain-limiting points (anterior, posterior, superior, inferior, left, and right) will then be picked to place images into the standard Talairach three-dimensional space [92]. After coregistering and fitting the three image sequences, a multimodal tissue classification will be performed using a Bayesian classifier based on discriminant analysis. This segmentation method automatically generates thresholds permitting the discrimination of grey and white matter as well as cerebrospinal fluid.

#### Hippocampus

The hippocampus will be traced manually on the coronal plane as described by Pantel et al [93]. Tracings begin with the generation of auxiliary guideline traces on the sagittal plane. The auxiliary traces are necessary to provide a neuroanatomically correct separation of rostral and caudal parts of the hippocampus from adjacent nonhippocampal brain tissue. Tracing will begin on the most medial slices. The starting slice is identified by choosing the slices that (going from medial to lateral) first show the cerebral peduncle separated from the upper pons. Once the anterior border of the hippocampus is identified on the starting slice, the vertical crosshairs will be placed anteriorly to this border. This procedure facilitates the identification of the anterior border on the following slices, because the head of the hippocampus, in general, does not extend beyond this level on the more lateral slices. The anterior border is outlined by the alveus and the uncal recess, which may be obliterated. Dorsally, CSF of the temporal horn of the lateral ventricle outlines the body, whereas the pulvinar thalamus serves as the border for the tail. On the medial slices the body is bordered by the fimbria, which is excluded from the trace itself. The posterior border is formed by the CSF of the lateral ventricle. The ventral border is defined by the WM of the temporal lobe.

#### Orbitofrontal cortex

The orbitofrontal cortex (OFC) will be outlined according to the proposed geometrical method developed by Lacerda et al [49]. The OFC will be manually measured in the coronal plane. The tip of the genu of corpus callosum will be located in the sagittal plane and used as the most posterior slice to be traced in the coronal plane. The last slice traced will be the most anterior coronal slice where brain tissue can be identified. The superior limit will be divided in two parts to reflect more the actual anatomical boundary of the OFC. In the subgenual regions, and specifically from the tip of the genu to the most anterior part of the CC, the superior boundary will be represented by the inferior border of the anterior cingulate corresponding to a midpoint at the interhemispheric fissure about five slices (5.08 mm) below the intercommissural line. More anteriorly, and specifically in the slices ahead of the genu of the CC, the superior limit will be represented by a midpoint placed on the intercommissural line. This "lowering" of the superior limit will be done to avoid inclusion of subgenual structures in the first slices that are not traditionally considered to be part of OFC (e.g., anterior cingulate).

In all slices, horizontal and vertical crosshairs will be placed as tangent lines at the inferior and lateral surfaces of the frontal lobes, respectively. The intersection of these two lines (horizontal and vertical crosshairs) will generate two lateral points that will be connected to the superior limit point, composing the lateral boundaries of the tracings. The inferior border will be traced following the inferior surface of the frontal lobes between the two lateral boundaries described above. The OFC will also be subdivided into gyrus rectus and orbital gyri by tracing a line through the olfactory sulcus. This subdivision will not be conducted in the most anterior slices where the olfactory sulcus disappears.

#### SPECT scans of Dopamine Transporter

The kits of TRODAT-1 were obtained through a scientific collaboration with the Research Institute of Nuclear Energy, Lung-Tan, Taiwan. The metastable technetium-99 was produced by a generator of [99Mo] (molybdenum-99) from the Institute of Nuclear Energy Research (IPEN-SP) with freshly elution. The kits of TRODAT-1 were marked with [99mTc] according to the technique developed by Kung et al[94]. Sixty mCi of elution of Sodium Pertechnetate [99mTc] diluted in 5 ml of saline solution are injected in the kit and submitted to 16 atmospheres and temperature of 120°C, during 30 minutes in an autoclave. Later, the solution of [99mTc] TRODAT-1 is cooled at room temperature.

The images will be acquired through a single photon emission computerized tomography (SPECT) Gama camera of the type (Hawkeye General Electric Medical System, USA) according to the methodology previously validated [95]. All subjects will receive an intravenous injection of 2 ml containing among 22 to 25 mCi of [99mTc]-TRODAT-1 in an antecubital peripheral vein. Images will be acquired 4 hours after the injection. The SPECT modality of the system with two heads and fan-beam collimators of ultra-high resolution will be used. Energy Window will be 140 ± 14 keV and matrix of 128 × 128 in circular orbit with step and shoot movements of 64 steps for each head will be used, with diameter and degree of rotation of 30 cm and 360°, respectively. The time of acquisition for the projection will be of 20 seconds, with a factor of zoom of 1.45. The reconstruction of the SPECT images will be accomplished through a filter algorithm of filtered retroprojection and a Butterworth filter of 0.4 cut off with pixels of 10th order. Three-dimensional images of the whole brain will be obtained and, for the analysis, two transaxial slices will be used at the level of the striatal body, with 3 mm of thickness corresponding to the level of the largest captation of the radiotracer. DAT density will be calculated with binding potential (DAT-BP) using regions of interests (ROI) bilaterally drawn in the striatum (STR) and the occipital cortex (OCC-background). BP will be calculated with the formula striatum (STR-OCC)/OCC.

#### Data management and Analyses

1) Questionnaires will be double typed and data will be entered on SPSS software data files. Participants will be divided into two categories, according to the diagnosis: (1) lifetime diagnosis of PTSD and (2) Traumatic experience, but no lifetime diagnosis of PTSD. The following comparisons will be carried out in the two groups:

1) Neuropsychological Study: neuropsychological measures of PTSD cases compared to controls;

2) Magnetic resonance imaging study: to assess neurostructural abnormalities in OFC and hippocampus of patients with PTSD compared to resilient controls;

3) Molecular neuroimaging study: dopamine transporter density using single photon emission tomography of PTSD cases compared to controls.

Data will be codified and analyzed using the Statistical Package for Social Sciences (SPSS for Windows, version 15.0). Proportion differences will be compared using the Chi Square test or Fisher's exact test, as appropriate. Continuous variables will be compared by Analysis of Variance (ANOVA) or Mann-Whitney test for non-parametric data. All significant tests will be considered as 2-tailed. P values < 0.05 will be considered statistically significant. Because of the exploratory nature of the study, we do not consider alpha adjustment in multiple comparisons and we did not calculate the sample size (Table 3). The main analyses will examine the relationship between exposure to traumatic events and the PTSD occurrence. Unadjusted relative risk for studied variables cognition, cortisol level, hippocampal volume, and dopamine transporter density (and 95% confidence intervals) are presented for trauma without PTSD and trauma with PTSD, both with and without adjustment for age (18–29 years, 30–39 years, 40–49 years, 50–60) and gender. As a secondary analysis, we will be adjusting for clinical and demographic variables previously associated with PTSD: marital status, country of birth, socio-economic status, urbanicity and employment status.

**Table 3 T3:** Sample size in each study for PTSD cases and control groups

	Neuropsychological study		Structural Neuroimaging study		Molecular Neuroimaging study	
	
	Case	Control	Case	Control	Case	Control
Number of individuals for each group	100	100	60	60	25	25

PTSD = Posttraumatic stress disorder; MRI = Magnetic Resonance Imaging

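### The named adjustments for hippocampal and orbitofrontal volume leave out head size; unless volumes are measured in size-normalised space, which is not stated, this costs precision and leaves an avoidable confounder

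*Protocol article*

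**What the plan says.** All references are to the protocol article.

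- **Comparison.** In Data management and Analyses, the structural study is "to assess neurostructural abnormalities in OFC and hippocampus of patients with PTSD compared to resilient controls". The sections Hippocampus and Orbitofrontal cortex describe manual tracing of both regions.
- **Test.** "Continuous variables will be compared by Analysis of Variance (ANOVA) or Mann-Whitney test for non-parametric data". "All significant tests will be considered as 2-tailed", and "P values < 0.05 will be considered statistically significant".
- **Adjusted analysis.** The section promises "Unadjusted relative risk for studied variables cognition, cortisol level, hippocampal volume, and dopamine transporter density", "both with and without adjustment for age (18–29 years, 30–39 years, 40–49 years, 50–60) and gender". Hippocampal volume is on that list; orbitofrontal volume is not.
- **Secondary analysis.** Further adjustment is for "marital status, country of birth, socio-economic status, urbanicity and employment status".
- **Segmentation.** The section Magnetic Resonance Imaging plans a tissue classification "permitting the discrimination of grey and white matter as well as cerebrospinal fluid". The same section places the images in Talairach space by means of six brain-limiting points. It does not say whether volumes are then taken in native or in scaled units.

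Intracranial volume, total brain volume and head size are not mentioned anywhere in the article.

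**The concern.** A regional brain volume can be expected to vary with the size of the head. If volumes are taken in native space and compared with no head-size term, there are two consequences. Between-person variation in head size stays in the error term, so the test is less precise than the same scans allow. And if cases and controls differ systematically in head size, part of that difference appears as a difference in hippocampus or orbitofrontal cortex. Cases and controls are not randomised, so such a difference cannot be ruled out by design.

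The geometry of the orbitofrontal tracing makes the dependence plain: its boundaries are tangents to the frontal lobe surface joined to a midpoint, so a larger frontal lobe gives a larger traced region. The SPECT outcome, by contrast, is scaled to a reference region. No equivalent is stated for the structural outcomes, which belong to one of the project's three main objectives.

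**Working it through.** The article gives no power, effect size or standard deviation and says that no sample size was calculated, so there is no stated figure to reproduce. What can be checked is the consequence of leaving head size out.

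**Inputs from the article**
- Two-sided test at 0.05 (Data management and Analyses).
- 50 per group (Abstract) or 60 per group (Table 3). The two figures disagree and need reconciling; both are carried here, and the point does not depend on which is right.

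**Assumptions, not in the article**
- True regional difference d = 0.5 SD before head-size adjustment.
- Within-group correlation r of regional volume with intracranial volume, given age and sex: 0.2, 0.3 or 0.5.
- For the confounding calculation only, a systematic head-size difference g between groups of 0.2, 0.3 or 0.5 SD.

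**Step 1: precision.** With head size as a covariate, residual variance is multiplied by 1 − r², so the effective difference is 0.5/√(1 − r²). The non-centrality is that value × √(n/2), and power comes from the two-sample t-test. The degree of freedom used by the covariate changes these figures by 0.1 point at most.

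| r | 1 − r² | Effective d | Power, 50 per group | Power, 60 per group | Equivalent n for 50 / 60 |
|---|---|---|---|---|---|
| no adjustment | 1 | 0.500 | 69.7% | 77.5% | 50 / 60 |
| 0.2 | 0.96 | 0.510 | 71.4% | 79.2% | 52 / 62.5 |
| 0.3 | 0.91 | 0.524 | 73.7% | 81.3% | 55 / 66 |
| 0.5 | 0.75 | 0.577 | 81.6% | 88.0% | 67 / 80 |

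Example: at r = 0.5 and n = 50, 0.5/√0.75 = 0.577, and 0.577 × √25 = 2.89, which gives 81.6%. The gain is about 2 points at r = 0.2, 4 at r = 0.3, and 12 (n = 50) or 10 to 11 (n = 60) at r = 0.5.

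**Step 2: systematic head-size difference, no true regional effect.** The spurious regional difference is r × g SD and its standard error is √(2/n), which is 0.200 at n = 50 and 0.183 at n = 60. The two-sided error rate (normal approximation) is Φ(rg/SE − 1.96) + Φ(−rg/SE − 1.96).

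| r | g | Spurious difference | Error rate, n = 50 | Error rate, n = 60 |
|---|---|---|---|---|
| 0.3 | 0.2 | 0.06 SD | 6.0% | 6.2% |
| 0.3 | 0.3 | 0.09 SD | 7.4% | 7.8% |
| 0.5 | 0.2 | 0.10 SD | 7.9% | 8.5% |
| 0.5 | 0.3 | 0.15 SD | 11.7% | 13.0% |
| 0.5 | 0.5 | 0.25 SD | 24.0% | 27.8% |

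**Step 3: chance imbalance.** At 50 per group, a head-size imbalance of 0.2 SD is one standard error, so an imbalance at least that large arises in about 32% of samples (27% at 60). At r = 0.5 an imbalance of 0.2 SD shifts the estimate by 0.5 × 0.2 = 0.10 SD. Averaged over samples this is already part of the standard error, and the 5% error rate holds.

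**The case against.** The case on the other side has real substance.

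- **The covariate list is not closed.** A reader might infer that Data management and Analyses sets out every adjustment, and so rules head size out. The article does not support that. Its Discussion also calls for depression measures as covariates, and its Background speaks of controlling for alcohol consumption, depression and illness; none of these is in the analysis section. That section is shared text for three studies. What stands is narrower: a test and a set of adjustments are stated, and head size is in neither.
- **The Talairach step may already normalise size.** If volumes are taken in scaled space, head size is at least partly removed. So it cannot be said flatly that the volumes will be compared without regard to head size. The measurement space is simply unstated.
- **The specificity question is a different one.** A reader might link head size to the article's question of specificity. That question sets PTSD against trauma exposure, stress or substance abuse, not regional against global loss, and head-size adjustment does not answer it.
- **Intracranial volume does not capture global atrophy.** Lost tissue is replaced by CSF, so the sum of grey matter, white matter and CSF changes little.
- **Matching and gender adjustment do part of the work.** The Abstract describes age- and sex-matched controls for the neuropsychological study and introduces the structural study as similar. This removes between-sex differences in head size, not within-sex variation. The correlation that matters is therefore the one given age and sex, and its value is not known here.
- **Chance imbalance is not bias.** The raised error rates in Step 2 need a fixed group difference in head size, for which the article gives no evidence.
- **The study is declared exploratory.** No stated power is missed. But that label is given as the reason for no multiplicity adjustment and no sample size calculation; it is not a reason to leave out a covariate that planned data can supply.

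**Conclusion.** The point holds as an inexpensive improvement to a stated method, not as proof of a biased analysis. The article names a test and adjustments for the structural outcomes that do not include head size, and it does not name orbitofrontal volume in the age- and gender-adjusted analysis at all. If volumes are in native space, an ANCOVA using the planned tissue classes is more precise and removes a possible confounder.

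The size rests on assumed values. At d = 0.5, power rises from about 70% to 71%, 74% or 82% with 50 per group, and from about 78% to 79%, 81% or 88% with 60, for r = 0.2, 0.3 or 0.5. At the low end the gain is slight. The error rate exceeds 5% only if the groups truly differ in head size; chance imbalance moves the individual estimate and nothing more. If volumes are measured in scaled space, much of the concern may fall away, which is why that statement comes first in the fix.

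**What to change.** 1. State in Magnetic Resonance Imaging whether hippocampal and orbitofrontal volumes are measured in native or in scaled Talairach space.
2. If native, state in Data management and Analyses that the main structural comparison is an ANCOVA of each hippocampal and orbitofrontal volume on group, with intracranial volume (grey matter + white matter + CSF from the planned BRAINS2 segmentation), age and sex as covariates. Report unadjusted volumes as supportive.
3. Say in the interpretation that this deals with head size only. It does not separate regional from global tissue loss, nor PTSD from trauma exposure.

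The cost is one or two sentences and no new scan. The article does not say that the three tissue classes will be summed, but the sum follows from the classification it already plans.

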**Methods and design:**

Cases and controls will be identified through an epidemiologic survey conducted in the city of São Paulo. Subjects exposed to traumatic life experiences resulting in posttraumatic stress disorder (cases) will be compared to resilient victims of traumatic life experiences without PTSD (controls) aiming to identify biological variables that might protect or predispose to PTSD. In the neuropsychological case-control study, 100 patients with PTSD, will be compared with 100 victims of trauma without posttraumatic stress disorder, age- and sex-matched controls. Similarly, 50 cases and 50 controls will be enrolled for the structural study and 25 cases and 25 controls in the functional neuroimaging study. All individuals from the three studies will complete psychometrics and a structured clinical interview (the Structured Clinical Interview for DSM-IV and the Clinician-Administered PTSD Scale, Beck Anxiety Inventory, Beck Depression Inventory, Global Assessment of Function, The Social Adjustment Scale, Medical Outcomes Study 36-Item Short-Form Health Survey, Early Trauma Inventory, Clinical global Impressions, and Peritraumatic Dissociative Experiences Questionnaire). A broad neuropsychological battery will be administered for all participants of the neuropsychological study. Magnetic resonance scans will be performed to acquire structural neuroimaging data. Single photon emission computerized tomography with [(99m)Tc]-TRODAT-1 brain scans will be performed to evaluate dopamine transporters.

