Despite the unquestionable progress in identification of neurocognitve and neuroanatomical abnormalities associated with PTSD over the past decade or so, it remains unclear whether neurostructural and neuropsychological alterations are specific to PTSD or are related to unspecific environmental factors such as stress and substance abuse. The findings from this neuropsychological study, together with data from neurostructural investigation, may offer an uncommon opportunity to examine the convergence of cognitive and neuroanatomical alterations in patients with PTSD. Stress-induced functional and structural alterations in hippocampus and OFC may mediate many of the symptoms of PTSD that are related to memory dysregulation and hyperexcitability. Interestingly, reversion of both neuropsychological and neuroanatomical abnormalities has been demonstrated after treatment with paroxetine, which in turn has been shown to promote neurogenesis in animal studies [97]. The increasing use of sophisticated neuroimaging techniques is certainly enhancing our understanding of PTSD, potentially improving prevention, treatment, and cognitive rehabilitation programs [23].

Although a previous study showed involvement of DAT gene in PTSD [67], and other indirect investigations have suggested a connection between dopaminergic system and stress [61], insufficient research has been done on the role of the DAT in relation to PTSD. To the best of our knowledge this will be the first SPECT study investigating dopamine transporter density in patients with PTSD and well matched resilient controls coming from an epidemiologic sample. The results of this study will help to disentangle whether possible dopaminergic changes in PTSD are a "state condition" or a "trait" marker of this disorder, raising a discussion why some subjects exposed to trauma develop PTSD and some others do not. Moreover, further studies evaluating patients with PTSD, resilient controls and healthy control subjects (who never experienced trauma) would provide useful information to clarify whether dopaminergic abnormalities are related to PTSD itself or to psychological trauma exposure.

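### Controls are matched on age and sex, but the stated tests for continuous outcomes leave both factors out, which makes them conservative and costs power

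*Protocol article*

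**What the plan says.** **Matching.** The Abstract (Methods and design) says that the PTSD patients in the neuropsychological study will be compared with "100 victims of trauma without posttraumatic stress disorder, age- and sex-matched controls". It introduces the structural and molecular studies with the word 'Similarly'. The Discussion describes the SPECT comparison as one made "in patients with PTSD and well matched resilient controls coming from an epidemiologic sample", without naming the matching factors. The Sample section and Tables 1 and 2 do not describe the matching: they give no ratio, no age tolerance, and nothing on whether pairs were formed or only the group distributions balanced.

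**Tests.** Data management and Analyses states: "Continuous variables will be compared by Analysis of Variance (ANOVA) or Mann-Whitney test for non-parametric data". For binary variables: "Proportion differences will be compared using the Chi Square test or Fisher's exact test, as appropriate". The tests are two-sided at 5% ("All significant tests will be considered as 2-tailed"; "P values < 0.05 will be considered statistically significant").

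**Adjustment.** The same section plans relative risks with 95% confidence intervals for cognition, cortisol, hippocampal volume and dopamine transporter density, "both with and without adjustment for age" (in four bands) and gender. Further demographic covariates are labelled secondary. No sample size was calculated.

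**The concern.** Matching makes cases and controls alike on age and sex. If those factors predict the outcome, the two group means tend to move together, and their difference varies less than it would between two independent samples. ANOVA and Mann-Whitney, used as stated, do not credit this. Variation due to age and sex stays in the error term, the standard error is overstated, and the p-value is too large.

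What is at stake is missed differences. The Background describes a literature with conflicting null results on memory and attention, and the Discussion hopes to settle some of the discrepancies with a better controlled sample. With no sample size calculation there is no known power margin to give away.

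**Working it through.** The protocol states no power, effect size or standard deviation, so there is no figure of its own to reproduce. The check asks what ignoring the matching costs.

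**From the documents:** two-sided alpha 0.05. Per group, n = 100 (neuropsychological), 25 (molecular), and 50 in the Abstract or 60 in Table 3 (structural). That last disagreement is a separate matter, so both values are shown.

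**Assumed, not in the documents:** the share ρ of outcome variance explained by age and sex, which under close matching is also the correlation between matched subjects, from 0 to 0.3. Standardised differences d are 0.4 (n = 100), 0.5 (n = 50 or 60) and 0.8 (n = 25).

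**Formulas (normal approximation, SD = 1):**
- SE used by the unadjusted test: sqrt(2/n)
- True SE under matching: sqrt(2(1−ρ)/n)
- Ratio of the two: 1/sqrt(1−ρ)
- Actual type I error: 2[1 − Φ(1.96 × ratio)]
- Power, unadjusted: Φ[(d − 1.96·sqrt(2/n)) / sqrt(2(1−ρ)/n)]
- Power, matching respected: Φ[d / sqrt(2(1−ρ)/n) − 1.96]

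**Worked case, n = 100, d = 0.4, ρ = 0.3.** The SE used is sqrt(0.02) = 0.1414 and the true SE is sqrt(0.014) = 0.1183, a ratio of 1.195. Unadjusted power is Φ[(0.4 − 0.2772)/0.1183] = Φ(1.04) = 85.0%. With the matching respected it is Φ(3.38 − 1.96) = Φ(1.42) = 92.2%.

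| ρ | SE ratio | Actual type I | Power n=100, d=0.4 | n=60, d=0.5 | n=50, d=0.5 | n=25, d=0.8 |
|---|---|---|---|---|---|---|
| 0 | 1.000 | 5.0% | 80.7 → 80.7 | 78.2 → 78.2 | 70.5 → 70.5 | 80.7 → 80.7 |
| 0.1 | 1.054 | 3.9% | 82.0 → 84.6 | 79.4 → 82.3 | 71.5 → 75.0 | 82.0 → 84.6 |
| 0.2 | 1.118 | 2.8% | 83.4 → 88.5 | 80.8 → 86.5 | 72.7 → 79.8 | 83.4 → 88.5 |
| 0.3 | 1.195 | 1.9% | 85.0 → 92.2 | 82.4 → 90.5 | 74.1 → 84.8 | 85.0 → 92.2 |

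Power is in percent, unadjusted → matching respected. The n = 25 and n = 100 columns agree because d·sqrt(n) = 4 in both.

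**Simulation check** (3,000 runs per setting; same sex, ages within 2 years). With n = 100 and no true difference, ANOVA rejected in 3.8%, 2.8% and 2.0% of runs at ρ = 0.1, 0.2 and 0.3, and Mann-Whitney in 4.1%, 3.0% and 1.9%. Power at ρ = 0.3:

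| Analysis | n=100, d=0.4 | n=25, d=0.8 |
|---|---|---|
| ANOVA | 85.5% | 82.7% |
| Mann-Whitney | 82.3% | 79.9% |
| Paired t-test | 92.0% | 90.0% |
| Linear model: group, sex, the protocol's four age bands | 92.0% | 90.7% |

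Adjusting for age and sex therefore recovers essentially all of the loss without any pairing. Chi-square and Fisher tests were not simulated.

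**Do the adjusted relative risks fill the gap?** Objective 2 and the second listed comparison name orbitofrontal cortex as well as hippocampus, but the list of variables for the relative risks has only hippocampal volume. For orbitofrontal volume the unadjusted test is the only analysis stated. Objective 3 asks whether transporter density is lower in cases. That is a difference in level, and a relative risk of PTSD does not estimate it.

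**The case against.** The best defence is that the plan already adjusts for exactly the two matching factors. The age- and gender-adjusted relative risks follow directly on the sentence about the main analyses, touch all three studies, and carry the only confidence intervals the article names. Adjusting for the matching factors is a valid way to analyse such a design. This stands for those relative risks and confines the point to the two-group tests and the unadjusted ratios. It does not reach orbitofrontal volume or the differences in level, and neither version of the ratio is named as the main one.

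A second defence is that the article condenses a fuller plan, that ANOVA can carry further factors, and that the Discussion speaks of depression measures as covariates. But the article does name its tests. It names no factor for the ANOVA and offers a plain two-sample rank test as the alternative.

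A reader might infer more than the documents support:
- *That paired tests are required.* Pair matching is never stated, and equal group sizes fit frequency matching equally well.
- *That the results would be invalid.* The error runs only towards caution, in a study that calls itself exploratory.
- *That odds ratios will be biased towards the null.* The article mentions no odds ratio, and an adjusted ratio is planned beside the unadjusted one.
- *That four age bands are too coarse.* In the simulation they did as well as pairing.
- *That SPECT is the clearest case.* Its matching factors are not named.

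**Conclusion.** The point holds as a loss of efficiency limited to the unadjusted comparisons. The stated tests for continuous outcomes do not use the factors on which controls were matched, and the adjusted relative risks do not replace them. The cost runs from nothing, if age and sex are unrelated to the outcome, to a standard error about 20% too large and 7–11 points of power if they explain 30% of its variance. At 10% it is 3–4 points. These figures rest on the assumed shares and effect sizes above and on close matching; the documents supply none of them. For the imaging studies they also rest on reading 'Similarly' and 'well matched' as age and sex matching. The plan should be changed because the remedy costs almost nothing, not because its false-positive rate is at risk.

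**What to change.** 1. State how matching was done: individual pairs or frequency matching, on which factors, and in which of the three studies.
2. Make the main comparison of each continuous outcome, orbitofrontal volume included, a linear model (ANCOVA) with PTSD group, age and sex, and report the adjusted difference with its 95% confidence interval. Where the outcome is clearly non-normal, fit the model to ranks or a transformed outcome. Add a matched-pair term only if individual pairs were formed.
3. For ratio estimates, name the age- and sex-adjusted version as the main result. Use conditional logistic regression only if pairs were formed.
4. Keep the unadjusted ANOVA, Mann-Whitney, chi-square and Fisher tests as descriptive.

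The cost is wording in the analysis section. Age and sex are needed for the matching in any case, so no extra data are required, and the models are standard. In the smallest study, with 50 subjects, age as a linear term plus sex takes the residual degrees of freedom from 48 to 46; the four bands plus sex take them to 44.
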